## Data analysis

1. Descriptive statistics on standard of care will be calculated, including percentage of centers meeting each structure criterion, percentage of subjects enrolled, dropped out, completion of the programme, receiving criterion process, investigations and referral per protocol, and percentage of subjects achieving the criterion outcome.
2. The change in clinical, service, and patient reported outcomes after the PEP programme at baseline, 6, 12, 36 and 60 months will be compared by paired sample t-test. The audit cycle will be repeated annually over a period of 5 years.
3. Independent sample t-test or Chi square test as appropriate will be used to compare the clinical and service utilization outcomes between PEP patients and controls.
4. Independent sample t-test or Chi square test as appropriate will be used to compare the clinical and service utilization outcomes between results in achieved in different audit cycles.
5. Cost effectiveness analysis (CEA) by mathematical modeling will be carried out by using cost and clinical outcome data provided by the HA, as well as quality-of-life and private service utilization cost data collected by the telephone surveys.

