**Abstract**

**Objectives:** The aim of this study is to evaluate the quality of care (QOC) of the Hospital Authority’s (HA) patient empowerment programme (PEP) programme using an evidence-based structured and comprehensive evaluation framework to identify areas for quality enhancement.

**Design, Setting and Subjects:** A longitudinal study will be conducted using the Action Learning and Audit Spiral methodologies to measure whether the target standard of care intended by the PEP programme is achieved. Each PEP participating clinic and non-government organization (NGO) will be invited to complete a structured evaluation questionnaire. The data of all patients who have enrolled into the PEP for more than one year will be included in the evaluation on the process and outcomes of care. To determine a difference of programme performance and impact between group (PEP participants and non-participants), cohort study would be adopted. A cohort includes all eligible DM patients under care of HA GOPC at 1 Sep 2009 will be followed up on the clinical outcomes including HbA1c, blood pressure, lipids, and complications rates. To evaluate the effect of PEP on patient-reported outcomes, 550 participants, as well as 550 of those who have not participated in the PEP, will be recruited from each cluster and followed up by telephone to evaluate the effect of the programme on quality of life (QOL), patient enablement, global rating of change in health condition and private service utilization at baseline, 6, 12, 36 and 60 months after enrolment. Data on the process of care will be retrieved from the HA medical records. The cost effectiveness analysis (CEA) by mathematical modeling will be carried out by using cost and clinical outcome data provided by the HA, as well as quality-of-life and private service utilization cost data collected by the telephone surveys.

**Main Outcome Measures:** The primary outcomes are the proportion of participants who have received the planned process of care and achieved the target HbA1c and blood pressure levels.

**Data Analysis:** Descriptive statistics on proportions meeting the QOC criteria will be calculated. The changes in clinical, service, and patient reported outcomes at 6 and 12 months will assessed by paired sample t-test for each audit cycle. The audit cycle will be repeated annually over a period of 5 years.

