## Hypotheses

The following hypotheses will be tested:

1. The criteria on structure and process should be achieved by all participating clinics and NGO;
2. More patients with DM will achieve the target HbA1c after 12, 24, 36 and 48 months in the PEP programme;
3. More patients with HT or DM will achieve the target blood pressure levels after 12, 24, 36 and 48 months in the PEP programme;
4. In longer terms, HT/ DM patients will have reduced cardiovascular risks and fewer complications;
5. Patients should report an improvement in quality of life (QOL), enablement and overall health condition after the PEP programme;
6. Patients who take part in PEP programme should not have any increase in service utilization rates.

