## Subjects

All patients who have been enrolled into the PEP programme will be included in the evaluation on process of care for each audit cycle; whereas all enrolled subjects who have been recruited for more than 12 months in the programme will be included in the evaluation on the clinical outcomes of care for each audit cycle.

To determine a difference of programme performance and impact between group (PEP participants and non-participants). A cohort of all eligible DM patients under care of HA GOPC at 1 Sep 2009 would be included for the monitoring of the changes in clinical and service utilization outcomes from Sep 2009 to Sept 2015.

550 patients who have enrolled into the PEP and 550 who have not taken part in the PEP will be invited in person from the general outpatient clinics by trained research assistants at the beginning of each evaluation cycle to take part in a telephone survey on patient reported outcomes for each cluster and written consent will be obtained (appendix A). All subjects who have given consent to the telephone follow-up survey will be interviewed by telephone within four weeks, at 6, 12, 36 and 60 months from recruitment to answer the SF-12 Health Survey on quality of life (QOL), the patient enablement Instrument, the Global Rating Scale (GRS) change in health, and a structured questionnaire on private service utilization rates.

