## Outcome measures

**Primary**

- The proportion of clinics/NGO that have satisfied each of the set structure criteria.
- The proportion of patients who have complied with the criterion process of care.
- The proportion of DM patients who have achieved a HbA1c level <7%.
- The proportion of HT/ DM patients who have achieved the target blood pressure.
- The estimated 10-year cardiovascular disease risk.

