# Implications

The results can:

1. provide empirical data on the QOC of PEP provided by the contractor (NGO) of HA;
2. provide evidence on whether the PEP can enhance patients on self-efficacy and knowledge of their diseases;
3. provide information on the effectiveness of PEP in improving the outcome of care for DM and HT patients, in order to guide policy decision making.

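### Hypotheses 2 and 3 (HbA1c and blood-pressure targets) name no comparator; no listed test is stated as a controlled comparison of change, and none is named as deciding

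*Protocol*

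**What the plan says.** Hypothesis 2 reads "More patients with DM will achieve the target HbA1c after 12, 24, 36 and 48 months in the PEP programme", and hypothesis 3 reads "More patients with HT or DM will achieve the target blood pressure levels after 12, 24, 36 and 48 months in the PEP programme". Neither names a comparison group. The matching primary outcomes are binary: "The proportion of DM patients who have achieved a HbA1c level <7" per cent, and "The proportion of HT/ DM patients who have achieved the target blood pressure".

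The Data analysis section then lists, among others:

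- **Item 2** states: "The change in clinical, service, and patient reported outcomes after the PEP programme at baseline, 6, 12, 36 and 60 months will be compared by" a paired t-test. It mentions no control group.
- **Item 3:** an independent t-test or chi-square test of clinical and service-use outcomes, PEP patients against controls. It mentions no baseline value, change or adjustment.

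The data-analysis paragraph of the Abstract gives descriptive statistics and one inferential method: "The changes in clinical, service, and patient reported outcomes at 6 and 12 months will assessed by paired sample t-test for each audit cycle".

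Under Subjects, the protocol sets up a cohort of all eligible diabetic (DM) patients in general outpatient clinics at 1 September 2009, to compare participants with non-participants. It "would be included for the monitoring of the changes in clinical and service utilization outcomes from Sep 2009 to Sept 2015". The Abstract lists HbA1c and blood pressure among that cohort's outcomes. Under Implications, the results are to "provide information on the effectiveness of PEP in improving the outcome of care for DM and HT patients".

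**The concern.** The study is meant to inform policy on whether PEP works, so the HbA1c and blood-pressure analyses need to separate a PEP effect from two other sources of difference.

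The first is movement over time that would have happened anyway, such as changes in usual clinic treatment or disease progression. Item 2 cannot remove it. The second is that participants and non-participants may differ from the start: under Background, patients enter PEP by consent, not by allocation. Item 3 does not remove this if it compares outcome levels at follow-up.

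The two tests can therefore disagree, and the protocol does not say which governs. Either could be reported as confirming the hypotheses. For patients with hypertension (HT) but no diabetes the position is weaker still, because the clinical comparison cohort excludes them while hypothesis 3, the blood-pressure outcome and the Implications section include them.

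**Working it through.** **The plan's own figure.** The only sample size given is for quality of life: 2 × (1.960 + 0.842)² / 0.3² = 174.4, so 175 per group as stated. Four successive 25% losses give 175 / 0.75⁴ = 553, against 550 stated. It reproduces, but says nothing about HbA1c or blood pressure. For those the protocol gives no N, no proportion at target and no within-patient correlation, so everything below rests on assumptions.

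**What each test estimates.** Let g be the change in the proportion at target shared by both groups, b the baseline gap (PEP minus non-participants) and e the PEP effect.

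- Item 2, within PEP: g + e.
- Item 3, read as follow-up levels: b + e.
- Difference in change between groups: (g + e) − g = e, provided the two groups would otherwise have had the same trend.

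**Item 2 with e = 0.** Assume 45% at target at baseline and a latent within-patient correlation of 0.5. The share of patients whose status differs between the two times (discordance) is then about 0.33. For N patients and shared gain g, SE = √((0.33 − g²)/N), and the two-sided 5% test is significant with probability Φ(g/SE − 1.96) + Φ(−g/SE − 1.96). With g = 0.02:

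| N | SE | g/SE | Probability significant |
| --- | --- | --- | --- |
| 1,000 | 0.0182 | 1.10 | 0.20 |
| 5,000 | 0.0081 | 2.46 | 0.69 |
| 10,000 | 0.0057 | 3.48 | 0.94 |

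With g = 0.01 at N=1,000 the probability is only about 0.09, so the problem is small if the drift and the cohort are both small. Lower discordance raises the rates: for a 5-point gain at N=1,000, assumed discordance of 30% and 20% gives 0.82 and 0.94.

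**Item 3 as a follow-up-only chi-square with e = 0.** Assume the gap persists as 50% against 45%. At 1,000 per group, the null SE is √(2 × 0.475 × 0.525/1,000) = 0.02233 and the alternative SE is √((0.25 + 0.2475)/1,000) = 0.02230. The probability is Φ((0.05 − 1.96 × 0.02233)/0.02230) = Φ(0.28) = 0.61. The same formula gives 0.38 at 550 per group and above 0.99 at 5,000.

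**Which test decides.** Hypotheses 2 and 3 use months 12, 24, 36 and 48, and Appendix C collects clinical data at 0, 12, 24, 36 and 48. Item 2 uses 6, 12, 36 and 60. Item 2 is a t-test, while the outcomes are proportions; chi-square appears only in items 3 and 4. The hypotheses' before-after wording and the Abstract point to item 2. The outcome type and the purpose of the cohort point to item 3. The text does not settle it.

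**The case against.** A reader might infer that the plan will count any change shared with non-participants as a PEP effect. The documents do not support that. Item 3 and the DM cohort do compare HbA1c and blood pressure with non-participants, an equal shared change cancels in that comparison, and nothing says item 2 alone decides hypotheses 2 and 3.

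Three further points deserve weight. First, this is an audit-spiral evaluation, and before-after change in enrollees is an ordinary audit quantity. The paired test is valid for the before-after null as worded; its significance becomes a false positive only when read as a programme effect. That stands, and it is why item 2 should be kept, but it does not cover the stated aim of informing on effectiveness.

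Second, item 3 may be meant as a test of changes, since the Subjects section says the cohort monitors changes, and a statistical analysis plan could specify this. That reading is possible. It still leaves the hypotheses without a comparator, the deciding test unnamed and HT-only patients without a clinical control.

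Third, comparing changes is not a complete cure. If patients with worse readings were more likely to enter PEP, regression to the mean would favour PEP. Background gives no such entry criterion. If the log-odds of entry rose by 0.2 per SD of worse baseline (other assumptions as above, no PEP effect), a test of changes would be significant about 19% of the time at 500 per group, about a third at 1,000 and over 90% at 5,000. This limit stands and belongs in the report.

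**Conclusion.** The concern holds in this form: hypotheses 2 and 3 are worded without a comparator; the only test stated as a change is uncontrolled; the only controlled test is unadjusted and not stated as a change; and no deciding test is named. For HT-only patients, no clinical control exists at all.

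The sizes are illustrations. The 20% and 69% for the paired test assume a 2-point shared gain and about 33% discordance; the 61% for the follow-up-only chi-square assumes a persistent 5-point gap. The protocol supplies none of these inputs. The clinical analysis takes in every enrollee beyond 12 months, so N may be large, and with a large N even modest drift or imbalance becomes significant. This should be corrected before analysis. It does not show that the plan is bound to reach a wrong conclusion.

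**What to change.** - **Hypotheses 2 and 3, in DM patients:** reword as a larger increase in the proportion at target among PEP participants than among non-participants in the Subjects-section cohort.
- **Data analysis (and the Abstract to match):** name the between-group difference in change from baseline in at-target status as the deciding test. One suitable model is a GEE logistic regression with group, month (0, 12, 24, 36, 48) and group-by-month, adjusted for recorded baseline characteristics. Report the result in percentage points as well, because equal point gains from unequal baselines are not equal on the log-odds scale.
- **Item 2:** keep the paired result as a descriptive audit figure.
- **HT-only patients:** report before-after change descriptively, and do not use it as evidence of effectiveness.
- **Report:** state that the contrast removes shared trend and fixed baseline gaps, but not differential regression to the mean or other time-varying confounding.

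The cost is rewording and one model. HbA1c and blood pressure are already to be followed in the whole cohort, so no new patients or visits are needed. The interval will be wider: with equal groups of 1,000 and discordance 0.33, the SE rises from √(0.33/1,000) = 1.8 points to √(2 × 0.33/1,000) = 2.6 points. Non-participants have no enrolment date, so a rule for assigning their index month must be written in advance.

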# Background

Diabetes mellitus (DM) and hypertension (HT) are major causes of morbidity and among the top 10 causes of deaths in Hong Kong in 2008 (Department of Health 2009). The Hospital Authority (HA) has initiated service improvement through introducing the patient empowerment programme (PEP) to improve the quality of care (QOC) for DM and HT patients. The evaluation on the QOC is an essential part of the programme in order to inform future policy. The Family Medicine Unit (FMU) of the University of Hong Kong (HKU) has been appointed by the HA to carry out the evaluation of the QOC of the programme.

The PEP programme invites non-Government organizations (NGO) with experience in community medical service and education to deliver empowerment sessions to enhance patients’ disease specific knowledge and self-management skills, self-efficacy and lifestyle modification. Eligible patients who are ambulatory, have stable mental and emotional conditions, and follow up at general outpatients clinics (GOPC) and family medicine specialist clinics (FMSC) regularly will be recruited for the PEP programme. Enrolled patients will receive generic and disease specific PEP sessions provided by the NGO. Patients will be excluded if they have severe heart failure, end stage renal failure (ESRF) or advanced eye diseases, are unable to understand or communicate in Chinese language, or refuse to give consent.

Studies have found that patient empowerment programmes are effective, especially those that include active patient involvement (Lorig and Holman 2003), in improving outcomes and are somewhat cost-effective. Although more studies would be needed to determine long-term benefits and the cost-effectiveness in both hard and soft indicators (i.e. health care utilization costs vs. less tangible measures of outcome, including quality of life (QOL) and self efficacy. Two trials in Hong Kong indicated the empowerment approach was applicable to the Hong Kong Chinese population (Chan, Chan et al. 2007; Siu, Chan et al. 2007).

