## Sample size calculation

The sample size for the evaluation on QOL change is estimated to detect a minimally clinically important difference (MCID) in health-related quality of life (HRQOL) studies, which is equivalent to Cohen’s small effect size of 0.3 (Cohen 1988). A sample size of 350 patients in total (175 PEP participants and 175 non-participants) is needed in order to have 80% power and 95% confidence interval estimated by independent t-test to detect a small effect size (Erdfelder, Faul et al. 1996). Therefore, 1100 patients (550 PEP participants and 550 non-participants) will need to be recruited to account for 25% dropouts each follow-up (4 times).

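### The comparisons of PEP patients with controls, and of audit cycles, use independent-sample tests that make no allowance for NGO, clinic or repeated patients, so their standard errors are miscalibrated

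*Protocol*

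**What the plan says.** Under Data analysis, item 3 compares PEP patients with controls and item 4 compares audit cycles. Both use the same wording, "Independent sample t-test or Chi square test as appropriate will be used to compare", and both are limited to clinical and service utilisation outcomes. Neither mentions stratification, a random effect or a robust variance.

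The Sample size calculation covers a different outcome, health-related quality of life in the telephone survey. It asks for 350 evaluable patients, 175 per group, to give "80% power and 95% confidence interval estimated by independent t-test to detect a small effect size". It then inflates to 550 per group for dropout alone.

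The protocol itself describes the grouping of patients:
- Background: "Enrolled patients will receive generic and disease specific PEP sessions provided by the NGO".
- Subjects: both survey groups are invited at the general outpatient clinics, for a "telephone survey on patient reported outcomes for each cluster".
- Outcome measures: the first primary outcome is a proportion of clinics and NGOs, so these units are audited separately and may differ.

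Subjects also places every patient with more than 12 months in the programme in the clinical evaluation of each audit cycle. Appendix C, the extraction form, lists no clinic or NGO identifier.

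**The concern.** An independent t-test or chi-square test gives correct standard errors only if patients' outcomes are unrelated within each group. Patients taught by the same NGO share its staff and materials. That can make their outcomes alike whether or not sessions are held in groups, which the protocol does not say. Controls have no NGO, so nothing on their side offsets this variation.

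Clinic effects behave differently. Where both groups come from the same clinics in similar proportions, a clinic effect largely drops out of the difference. Where PEP uptake varies by clinic, part of it remains.

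At stake are the intervals and p-values for the HbA1c and blood-pressure target proportions, which are primary outcomes and are meant to inform policy. The record-based comparisons are large, but this does not cure the problem, because the variance inflation grows with the number of patients per NGO.

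**Working it through.** **The plan's own figure.** Inputs from Sample size calculation: effect size 0.3 (SD = 1), 80% power, 5% error taken as two-sided, 25% dropout at each of four follow-ups.
- n per group = 2 × (1.960 + 0.842)² / 0.3² = 174.4, rounded up to 175. This agrees with the plan.
- Dropout: 175 / 0.75⁴ = 553 per group, against 550 stated. Conversely, 550 × 0.75⁴ = 174 remain at the last survey, with 79.9% power (normal approximation).

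The stated 80% is therefore right if patients are independent.

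**NGO clustering in the PEP group only.** Assumptions, none from the protocol: ICC 0.01 to 0.05, equal groups, and m patients per NGO. The two values of m are 17.4 (174 patients over 10 assumed NGOs) and 100.
- Design effect in the PEP group: DE = 1 + (m − 1) × ICC.
- Variance of the difference relative to independence: F = (DE + 1) / 2.
- True two-sided error of the unadjusted test: 2 × [1 − Φ(1.96 / √F)].

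| m | ICC | DE | F | True error at nominal 5% |
|---|---|---|---|---|
| 17.4 | 0.01 | 1.164 | 1.082 | 6.0% |
| 17.4 | 0.05 | 1.820 | 1.410 | 9.9% |
| 100 | 0.01 | 1.990 | 1.495 | 10.9% |
| 100 | 0.05 | 5.950 | 3.475 | 29.3% |

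**Survey power under the same assumptions.** With 174 per group and m = 17.4, power = Φ(0.3 / √(2F/174) − 1.96).
- ICC 0.01: Φ(2.690 − 1.960) = about 77%.
- ICC 0.05: Φ(2.357 − 1.960) = about 65%.

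**Clinic effect shared evenly by both groups.** The clinic component cancels, so the variance of the difference is multiplied by (1 − ICC).
- Error of the unadjusted test = 2 × [1 − Φ(1.96 / √(1 − ICC))] = 4.9% at ICC 0.01 and 4.4% at 0.05.
- Power with 175 per group is 80.5% and 82.1%.

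The unadjusted test is then slightly conservative.

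**Audit cycles (item 4).** The same programme is compared over time, so clinics and NGOs are largely common to both sides and their effects partly cancel. The inclusion rule in Subjects also lets one patient appear in several cycles. An independent-sample test ignores that dependence too. The protocol gives nothing from which to size the net effect.

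**Survey size.** The Abstract and Subjects describe 550 + 550 for each Hospital Authority cluster (an administrative grouping), whereas Sample size calculation gives 1100 without that qualifier. With 174 evaluable per group in each of just two such clusters, 348 per group pooled, power would be 97.7% before any design effect.

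**The case against.** The strongest reply is that nothing in the protocol establishes the size of the problem. It gives no ICC, number of NGOs or patients per NGO. Patients are not allocated by clinic, and both survey groups come from the outpatient clinics, so the most obvious source of clustering largely cancels. This stands, and it is why the result is a conditional range. It does not remove NGO effects, which exist on one side only, or clinic effects left by uneven uptake.

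A second reply is that variance estimation is normally left to a statistical analysis plan, and one may exist. That would carry weight if the protocol were silent, but it names the tests.

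Two stronger readings are tempting, and the documents support neither:
- A reader might infer that the stated 80% power is wrong. It is correct on its own inputs. It also belongs to the quality-of-life survey, which items 3 and 4 do not cover. If recruitment is 550 + 550 per Hospital Authority cluster, pooled power could stay above 80% despite a design effect.
- A reader might apply the full design effect to the record data. At 100 patients per unit that gives an error of about 16% to 42%. It requires units that the compared groups do not share on either side, or controls that greatly outnumber PEP patients. The protocol states neither, and audit cycles largely share their units.

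**Conclusion.** The point holds in a limited form. Item 3 uses tests that ignore NGO effects confined to the PEP group and any clinic effects left by uneven uptake. Its standard errors are therefore miscalibrated: probably too small on account of NGOs, and slightly too large for a balanced shared clinic effect. With assumed ICC 0.01 to 0.05, equal groups and clustering among PEP patients only, the true error at a nominal 5% is about 6% to 10% at about 17 patients per NGO and about 11% to 29% at 100.

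Item 4 has the same omission, with a smaller effect of uncertain direction, and it also overlooks patients who recur across cycles. The 80% survey power should be read as conditional on no clustering. The survey's total size is itself unclear until the per-cluster wording is settled.

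**What to change.** 1. In Data analysis, replace the tests in items 3 and 4 with linear regression, or logistic regression for the target proportions. Use clinic as a stratum or random effect and an NGO random effect in the PEP group. Cluster-robust standard errors with a small-sample correction are an alternative.
2. In item 4, also allow for patients who contribute to more than one cycle.
3. Apply the same approach to the group comparison of quality of life.
4. Add clinic and NGO codes to the Appendix C extraction.
5. Reconcile 1100 in total with 550 + 550 per cluster in the Abstract and Subjects. Then state in Sample size calculation that 80% power assumes no clustering.

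The cost is revised analysis wording and two extra codes to extract. Because the data are supplied anonymised and the form lists neither code, their availability has to be confirmed with the data provider. Intervals may widen.

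### The comparison of PEP participants with non-participants uses only unadjusted tests, so it cannot separate selection into the programme from the effect of the programme

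*Protocol*

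**What the plan says.** The Abstract sets the between-group part of the study up as observational: "To determine a difference of programme performance and impact between group (PEP participants and non-participants), cohort study would be adopted". The Subjects section defines the source population: "A cohort of all eligible DM patients under care of HA GOPC at 1 Sep 2009 would be included", with changes in clinical and service-use outcomes followed from September 2009 to September 2015.

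Entry to PEP is not by random allocation. The Background lists among the exclusions patients who "are unable to understand or communicate in Chinese language, or refuse to give consent". Appendix B describes an e-referral system, and Appendix C counts patients identified as eligible, recruited and enrolled as separate steps.

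For this comparison, Data analysis item 3 names an independent t-test or "Chi square test as appropriate will be used to compare the clinical and service utilization outcomes between PEP patients and controls". Neither the other items in that list nor any other section mentions regression adjustment, matching, propensity scores, weighting, stratification or baseline comparability. The Implications section expects the results to "provide information on the effectiveness of PEP in improving the outcome of care for DM and HT patients" and so to inform policy.

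**The concern.** A two-sample t-test or chi-square test estimates a programme effect only if those who joined and those who did not would have had the same outcomes without the programme. Here patients pass through referral, recruitment and consent before they enrol. Each step may be related to glycaemic control, adherence and clinic attendance, which are close to the outcomes being compared. A difference found by item 3 could then reflect who was referred and agreed, what the programme did, or both, and the test cannot tell these apart.

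At stake is the between-group evidence on HbA1c and blood pressure target attainment, both listed as primary under Outcome measures, and on service use. A large cohort does not protect against this. It reduces random error and leaves the bias unchanged, so a modest selection difference can look conclusive.

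The gap cannot be put down to an analysis plan that is not shown. The protocol names the tests itself, and they are unadjusted.

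**Working it through.** **The plan's own figure.** The only sample size given is for quality of life: effect size 0.3, 80% power, and 95% confidence read as two-sided 5%. Per group, n = 2 × (1.960 + 0.842)² / 0.3² ≈ 174.4, rounded up to 175, as stated. Four successive losses of 25% give 175 / 0.75⁴ = 553, against the stated 550. The arithmetic holds and is not in dispute. It rests on the same independent t-test between participants and non-participants, so it shares the exchangeability assumption.

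**What cannot be computed.** The protocol gives no cohort size, baseline imbalance or relation between covariates and outcomes. No corrected estimate can be derived, and what follows is illustration under stated assumptions.

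**How a gap can arise without any effect.** Assume a trait, such as motivation, with target attainment of 60% among those who have it and 40% among those who do not. If 60% of participants and 50% of non-participants have it:

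- participants: 0.6 × 60% + 0.4 × 40% = 52%
- non-participants: 0.5 × 60% + 0.5 × 40% = 50%

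That is a 2-point gap with no PEP effect. If the trait is instead more common among non-participants (50% against 60%), the gap is −2 points, and a true benefit of 2 points would appear as zero.

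**What the crude test does with such a gap.** Assume attainment near 50%, a true effect of zero and a gap that persists. Then z = gap / √(2 × 0.25 / n), with n per group (assumed):

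| n per group | standard error | gap 2 points | gap 3 points | gap 5 points |
|---|---|---|---|---|
| 5,000 | 0.0100 | 2.0 | 3.0 | 5.0 |
| 10,000 | 0.0071 | 2.8 | 4.2 | 7.1 |
| 20,000 | 0.0050 | 4.0 | 6.0 | 10.0 |

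Expressed as the chance that a nominal 5% test rejects (normal approximation), a 2-point gap gives about 52% at 5,000 per group and 81% at 10,000. A 5-point gap gives over 99% at 5,000.

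**Whether change scores rescue it.** Item 3 does not say whether follow-up values or changes are compared.

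- Continuous outcomes: if changes are compared, a constant baseline gap cancels. Differing trajectories and regression to the mean do not.
- Target attainment: a chi-square test on the proportions at target takes no account of who was at target at the start.

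**Whether another item fills the gap.** Item 2 is a paired before-after test. It has no control group and is itself open to regression to the mean and secular trend, so it does not supply the missing adjustment.

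**The case against.** The strongest reply is that the study is mainly an audit against set standards. The Abstract defines the primary outcomes as proportions among participants, and Hypotheses 2 and 3 concern patients in the programme. Items 1 and 2 address these, so the between-group test is one component of the evaluation. This stands as a limit on scope. It does not help where the protocol uses the between-group contrast for impact and effectiveness.

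A reader might also infer more than the documents support:

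- **That the comparison measures who joined rather than what PEP did.** This cannot be shown. The contrast mixes the two, and neither the size nor the direction of the bias is known. If poorly controlled patients were referred preferentially, a real benefit could be hidden.
- **That being ambulatory, mentally stable and a regular attender separates the groups.** The comparison cohort consists of eligible patients, so on the natural reading these criteria apply to both sides. The argument rests on referral and consent.
- **That non-participants are known to be refusers or unreferred patients.** No section says why they did not take part.
- **That raw follow-up values are certainly what is tested.** The Subjects section speaks of monitoring changes, so that is only one reading.
- **That p-values would always be extremely small.** At the low end of the illustration, z = 2.0 corresponds to p of about 0.046.

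**Conclusion.** The point holds in this form: for a non-randomised comparison that it intends to read as programme impact, the protocol fixes only crude tests, and these cannot separate selection from programme effect in either direction. Following the plan as written can give a biased answer. The weakness is clearest for HbA1c and blood pressure target attainment, where baseline status is ignored. It is less severe for continuous outcomes if changes are analysed.

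The z range of 2.0 to 10.0 shows how readily a modest gap becomes significant. It depends on assumed group sizes, an assumed 50% base rate, an assumed gap of 2 to 5 points that persists in full, and no PEP effect. It is not an estimate of the bias in this study.

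**What to change.** Revise Data analysis item 3 as follows.

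1. Define an index date (month 0) for non-participants that is comparable to enrolment. Appendix C is built around recruitment and enrolment, and the protocol does not say what month 0 is for patients who never enrol.
2. Make the main between-group analysis a regression: linear for continuous outcomes, logistic for target attainment, and a count model for attendances. Adjust for the month-0 value of the outcome, age, sex, baseline HbA1c, blood pressure, LDL and BMI, prior-year attendances, existing complications and clinic. A propensity-score weighted or matched analysis on the same variables is an acceptable alternative.
3. Report baseline balance between the groups.
4. Keep the t-tests and chi-square tests as descriptive only.

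The cost is modest. HbA1c, blood pressure, LDL, BMI and attendances in the past 12 months are already on the Appendix C form. Age, sex, diagnosis codes (for existing complications) and clinic must be added to the extract, the index date must be constructed, and some programming is needed. No further patients or visits are required. Residual confounding by unmeasured factors such as motivation will remain, and the report must say so wherever effectiveness is claimed.
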